#### Baseline phase

The baseline phase will involve conducting baseline household surveys in each of the intervention clusters and in-depth interviews of OTCMS in both the intervention and control clusters.

##### Household survey:

A household survey will be conducted in the intervention arm to document pre-intervention malaria testing rates among children under 10 years visiting OTCMS for malaria treatment in the past 1 month preceding the survey. The household questionnaire will be completed by one individual per household, usually the primary caregiver. The questionnaire will contain modules on:
Background information and consentDetails of the respondentHousehold membersTreatment seeking of children under 10 years with a fever in the past 1 month preceding the surveyPractices of OTCMS visited by caregivers with children under 10 years with a fever (i.e., malaria test done, test results, and treatment given)Malaria preventive measures by caregivers

##### In-depth interviews:

In-depth interviews with OTCMS in the selected clusters in both study arms will be conducted to determine possible factors preventing the effective management of malaria at their level. Their knowledge on the following themes will be explored:
Symptoms of uncomplicated and severe malariaTest, treat, and track (T3) malaria initiativeAny previous skills on the use of mRDTsChallenges in managing malaria at their level

In-depth interviews with OTCMS in the intervention and control arms will be held at different times by the research team and recorded for reference purposes.

#### Intervention phase

Intervention activities for this study will be (i) facilitating acquisition of subsidized mRDT kits; (ii) training OTCMS on malaria diagnosis, treatment, and tracking of cases; (iii) quarterly supportive visits to OTCMS after training; (iv) community sensitization on malaria focusing on the T3 strategy; and (v) introduction of malaria surveillance tool for use by OTCMS.

##### Acquisition of subsidized mRDT kits:

The research team will facilitate the acquisition of subsidized mRDT kits from the National Malaria Control Programme. The mRDTs will be provided to all OTCMSs in the selected intervention clusters only. mRDTs will be supplied on monthly basis to the various OTCMS participating in the study based on inventory. The OTCMS will be able to contact the research team anytime they are about to run out of stock. Stock management records will be kept by the research team to monitor the distribution of mRDTs. For the sake of identification purposes, the mRDTs will be stamped and OTCMS will be advised to store them in a cool, dry place. mRDT kits will be provided at no cost to participating OTCMS. They will be asked to price the mRDTs at a cost not more than the market wholesale price of GH¢2.40/kit (~$0.44).

##### Training of OTCMS:

Added to the supply of mRDTs, OTCMS in the selected intervention clusters will receive provider training on malaria diagnosis, treatment, and follow-ups on their clients. This additional training will be conducted over 2 days and will contain six training modules on:
Knowledge on malariaOverview of national guidelines on malaria diagnosis, treatment, and preventionAppropriate treatment when test is positiveAppropriate actions and treatment when test is negativeEffective communicationImportance of good-quality data in malaria surveillance: this module will discuss how the informal private healthcare sector, by keeping accurate data, can contribute meaningfully to an efficient malaria surveillance system (see additional file for sample of surveillance tool).

##### Supportive visits to OTCMS after training:

In the intervention arm, support visits will be provided to each participating OTCMS during the implementation phase to monitor and assess what the providers are doing and to reinforce the skills acquired by providers during the earlier training workshop. During the support visits, where possible, investigators will observe providers attending to patients seeking treatment for fever. Questions on the different aspects of the training will also be asked. Based on their responses, guidance will be provided on areas where the provider is experiencing difficulty. Providers will be asked about possible challenges they are experiencing on implementing what they were taught during the training. mRDT kits will also be supplied during these visits and stock of mRDT recorded. The frequency of the visit will be once a month for the first quarter (3 months) of the deployment of intervention, and afterwards quarterly (every 3 months).

##### Community sensitization on malaria:

Public health education programs on malaria (cause, diagnosis, treatment, and prevention) according to the policies of the National Malaria Control Programme and Ghana Health Services will be carried out in all clusters of the intervention arm only. Community health workers will be used to carry out this health education in churches, mosques, and schools. Communities will be sensitized on the importance of demanding malaria testing before treatment. In addition to the community health workers, community town criers will also provide sensitization on market days.

##### Introduction of malaria surveillance tool:

A malaria surveillance tool (see additional file 2) will be introduced to OTCMS at the initial training on how to use mRDTs. They will be enlightened on the importance of the tool and also trained on how to keep accurate record of all suspected malaria cases attended to using the tool. At quarterly visits, OTCMS will be engaged to elucidate possible challenges and bottlenecks experienced on the use of this tool. The community will also be sensitized on the surveillance tool.

#### Evaluation phase

The evaluation phase will include mystery client surveys, assessment of OTCMS surveillance register, mRDT quality survey, and end-line household survey.

##### Mystery client survey:

Mystery client surveys will be used to support the evaluation of OTCMS conduct in implementing the T3 strategy. Mystery client (one who pretends to be a real patient) data collection will commence in the 4th month of the intervention period. The mystery client would also assess the quality of RDT use in the intervention arm. A total of 13 mystery clients will be recruited and given intensive training over 3 days on the clinical scenario and how to fill the assessment checklist/form (see additional file 3). Practical sessions will be included. Each OTCMS will be visited twice a month by a different mystery client for 3 months during the peak malaria transmission season (May–July).

The mystery client will present at the OTCMS’s shops saying that he/she had fever that he/she thought was like a malaria fever that he/she had experienced on a previous occasion. He/she will then observe the provider’s response whether RDT will be proposed or not before treatment. The outcome of interest for the mystery client assessment will comprise 6 key steps in conducting and interpreting an RDT for malaria:
Provider (OTCMS) proposes to do mRDT test.Use antiseptic in preparation for finger prick (to reduce the risk of infection, the mystery client will tactfully demand for the use of an antiseptic to prepare the finger before pricking if the provider does not do that).Read the result correctly (providers who accurately read a negative test, assuming that all mystery clients did not have malaria).Show the result to the client.Provide correct treatment according to the result (i.e., providers prescribe ACT for those who read a positive test result; refrained from giving any antimalarial drugs for a negative client).Cost of mRDT.

##### Assessment of OTCMS surveillance registers:

The OTCMS surveillance registers will be assessed for:
Symptoms warranting testingProportion of suspected malaria cases testedProportion of mRDT-negative cases given an ACT

##### mRDT quality survey:

As part of the evaluation phase, an mRDT quality survey will be conducted among suspected malaria patients visiting OTCMS in the selected intervention clusters during the peak malaria transmission season (May–October). Thick and thin blood smears for malaria microscopy will be prepared for eligible suspected uncomplicated malaria cases attended to by OTCMS. The microscopy results will be matched against mRDT results to determine the sensitivity, specificity, and predictive values of the mRDTs used.

##### Household survey:

The primary outcome will be measured through end-line household surveys. These will follow details of the baseline survey and will be conducted in both intervention and control arms.

### Sample size estimation

#### Mystery client survey

A total of 13 mystery clients will be recruited and trained. Each OTCMS will be visited twice a month by a different mystery client for 3 months (May–July). This will amount to a total of 48 visits in the intervention arm and 30 visits in the control arm.

#### mRDT quality survey

A minimum of 591 suspected uncomplicated malaria cases visiting OTCMS in the intervention clusters will be required for the mRDT quality survey based on an estimated sensitivity of 98.7% (unpublished national data), 1% precision, 20% non-response rate, and 95% confidence level.

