## Methods/design

### Study design

The proposed interventions will be evaluated using a two-arm (intervention and control), cluster randomized trial across 8 rural clusters (4 clusters per arm), in two adjacent districts of Ghana. The method of Wiseman et al. will be used in this study with some modifications [21]. Wiseman et al. used a three-arm stratified cluster randomized trial to evaluate the effectiveness and cost-effectiveness of two interventions designed to support the roll-out of mRDTs and improve the rational use of ACTs. They focused in part on private medicine retail outlets (known as OTCMS in Ghana), who are the focus of this study. Wiseman et al. looked at the effectiveness of individual interventions, but this study will evaluate the combined effectiveness of different interventions.

A cluster is defined as a geographical community which contains at least one OTCMS, and this will be the unit of randomization within each study arm.

The intervention arm has 8 clusters, and out of these, 4 will be randomly selected using a computer-generated list. The control arm has 4 clusters, and all these will be included in the study (Fig. 1). An urban sub-district (Begoro) in the intervention district will act as a buffer between the two arms. This method is adopted to reduce contamination (that is, filtering of information across the two arms) to the barest minimum. The selected four clusters per study arm will yield a total of 8 OTCMS in the intervention arm and 5 OTCMS in the control arm.

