### Data management and analysis

The principal investigator (PI) will ensure that all implementation and evaluation activities are according to standard operating procedures. Quality assurance will include training of field workers/data collectors few days before data collection. The training will involve practical sessions. During data collection period, field supervisors will monitor study implementation through weekly visits to sites.

All data collected will be anonymized using only study numbers and stored in locked cabinets after entry into a computer with a password known only to investigators. Data will only be made available to authorized persons such as members of the institutional review board. Data will be double entered and verified using Microsoft Access 2010 (Microsoft Inc., Redmond, Washington) database, and later imported into STATA version 12.0 (STATA Corporation, College Station, Texas) for analysis. Any discrepancies will be corrected using source documents. To account for correlation within clusters, the generalized linear mixed model (GLMM) technique of analysis will be used in this study. Estimates from the logistic regression model with random effect will be used to determine the intervention effect. Data (recordings) collected during in-depth interviews will be transcribed, translated, and analyzed using NVivo 12 by QSR International. This will provide a better understanding of the quantitative observations.

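### The 591 for the mRDT quality survey assumes independent patients, although all come from 8 shops in 4 communities, so the stated 1% precision for sensitivity is too optimistic

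*Protocol article*

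**What the plan says.** Under Sample size estimation, mRDT quality survey, the protocol article asks for "A minimum of 591 suspected uncomplicated malaria cases visiting OTCMS in the intervention clusters", a figure "based on an estimated sensitivity of 98.7% (unpublished national data), 1% precision, 20% non-response rate, and 95% confidence level". No design effect or intracluster correlation is mentioned.

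The mRDT quality survey paragraph of the Evaluation phase says where the patients come from: "an mRDT quality survey will be conducted among suspected malaria patients visiting OTCMS in the selected intervention clusters". Study design gives the number of units: "The selected four clusters per study arm will yield a total of 8 OTCMS in the intervention arm".

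Two other places deal with clustering. The household survey calculation, which follows directly, applies a variance inflation factor of 2.92, from an intracluster coefficient of 0.02 and an average cluster size of 97. Data management and analysis states: "To account for correlation within clusters, the generalized linear mixed model (GLMM) technique of analysis will be used in this study".

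Sensitivity, specificity and predictive values of the mRDTs are listed among the secondary outcomes. So is the percentage of OTCMS able to perform and interpret an RDT accurately.

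**The concern.** Patients tested at the same shop share kit storage, working conditions and the skill of whoever runs the test there. If these differ between shops, test errors cluster by shop, and 493 patients carry less information than 493 independent ones. The protocol has reason to expect such differences, since it makes accurate performance and reading of the test an outcome counted per OTCMS.

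The household survey is inflated for clustering, and its sample includes the same four intervention communities. The mRDT survey is not inflated. At stake is the precision claimed for a named secondary outcome: a reader would expect sensitivity to be known to within one percentage point, and an interval computed on the assumption behind the 591 would be too narrow.

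**Working it through.** **Inputs from the protocol.** Sensitivity p = 0.987, precision d = 0.01, 95% confidence (z = 1.96), 20% non-response; 8 OTCMS in 4 intervention communities.

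**Assumptions, not in the protocol.** An ICC for test sensitivity of 0.01–0.05 (the 0.02 given for the household survey lies in this range but describes another quantity), and a microscopy-positive share of 30–50%.

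**Step 1: reproduce the plan's figure.**
- n = z² p(1−p)/d² = 1.96² × 0.987 × 0.013 / 0.01² = 492.9, so 493.
- 492.9 × 1.2 = 591.5, stated as 591.

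The four stated inputs account for the whole figure, so the implied design effect is 1. (Dividing by 0.8 gives 617, which does not match. If 20% of 591 are lost, 473 remain and the half-width is 1.02 points, a negligible difference.)

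**Step 2: half-width with clustering, all 493 counted as the plan does.** DE = 1 + (m − 1) × ICC; half-width = 1.96 × √(0.987 × 0.013 × DE / 493).

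| ICC | 8 shops (m = 61.6): DE; half-width | 4 communities (m = 123): DE; half-width |
|---|---|---|
| 0 | 1.00; 1.00 | 1.00; 1.00 |
| 0.01 | 1.61; 1.27 | 2.22; 1.49 |
| 0.02 | 2.21; 1.49 | 3.44; 1.86 |
| 0.05 | 4.03; 2.01 | 7.11; 2.67 |

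Half-widths are in percentage points. Only ICC = 0 gives the stated 1.0.

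**Step 3: more patients from the same shops would not restore 1%.** As m grows, the half-width tends to 1.96 × √(0.012831 × ICC / k) for k units. At ICC 0.02 this floor is 1.1 points for 8 shops and 1.6 for 4 communities.

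**Step 4: the denominator that sensitivity actually has.** Sensitivity is estimated only in microscopy-positive patients. At ICC 0.02:

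| Assumed positive | Positives | No clustering | By shop: DE; half-width | By community: DE; half-width |
|---|---|---|---|---|
| 50% | 246.5 | 1.41 | 1.60; 1.79 | 2.21; 2.10 |
| 30% | 147.9 | 1.83 | 1.35; 2.12 | 1.72; 2.39 |

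Fewer positives per shop lower the design effect, but the half-width still grows. By shop, clustering adds 1.79 − 1.41 = 0.38 points at 50% positive and 2.12 − 1.83 = 0.29 at 30%.

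**Step 5: the symmetric interval breaks down here.** Only 1.3 points lie between 98.7% and 100%, so any half-width above 1.3 gives an impossible upper limit. A Wilson interval on the effective sample size avoids this. At 50% positive, ICC 0.02 and clustering by shop, the effective size is 246.5/1.60 ≈ 154, and the 95% interval around 98.7% runs from about 95.4% to 99.6%. Without clustering (n = 246.5) it runs from about 96.4% to 99.5%. The half-widths above therefore show the order of the loss and are not figures to print.

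**The case against.** The strongest objections concern size rather than direction, and most of them stand.

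- **The ICC is borrowed.** The 0.02 describes testing rates among children by community, not test sensitivity by shop. At 98.7%, an ICC of 0.02 implies a between-shop standard deviation of √(0.02 × 0.012831) ≈ 1.6 points, which is large against 1.3 points of headroom. Common supply, training and supervision would also reduce differences between shops. This stands: the documents do not give the size of the loss.
- **A single replacement figure is tempting.** A reader might infer that the true precision is ±1.5 to ±1.9 points (ICC 0.02, all 493 patients) and want that printed. The documents do not support it: it uses the wrong denominator and a borrowed ICC, and it yields upper limits of 100.2% to 100.6%.
- **The mechanism can be overstated.** A reader might infer that one seller stores the kits and performs and reads every test in a shop. No section says so, and the mRDT quality survey text does not say who reads the test. The point needs only that tests within a shop share conditions.
- **The analysis text is no firm contradiction.** A reader might take the mixed-model sentence as an instruction covering this survey, or assume that simple binomial intervals are planned. The model's estimates are tied to the intervention effect, whereas this survey is in one arm. No interval method for accuracy is stated, and one may sit in an analysis plan not shown.

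None of this rescues the stated 1%. That figure is printed without condition and rests on a design effect of 1.

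**Conclusion.** The point holds as a fault in a design assumption; the arithmetic of 591 is consistent with its inputs. The 1% precision is too optimistic for any positive within-shop correlation.

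The size depends on the assumed ICC and the assumed microscopy-positive share, neither of which the protocol states. Counting suspected rather than microscopy-positive patients is a related weakness that may cost more precision than clustering does, but the clustering loss remains once the denominator is corrected.

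Nothing here calls for a larger survey, and the primary comparison is untouched. No test or decision rule is tied to the accuracy estimates. Severity is minor.

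**What to change.** In Sample size estimation, mRDT quality survey:

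1. Keep the planned number and remove the unconditional 1% claim.
2. Restate the expected precision for the microscopy-positive denominator, naming the assumed positive share.
3. Declare a design effect by OTCMS and show the precision over a range of assumed ICCs, for example 0.01 to 0.05.
4. Use an interval that respects the 100% bound, such as Wilson or Clopper-Pearson on the effective sample size, rather than a symmetric plus-or-minus figure.

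In the analysis, report sensitivity, specificity and predictive values with intervals that allow for clustering by OTCMS.

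The cost is a few sentences and a shop identifier in the analysis file; no extra patients are needed. The stated precision becomes less favourable. The design effect for sensitivity will also be poorly estimated: at 98.7%, 493 positives would give about 493 × 0.013 ≈ 6 false negatives and 246 about 3, spread over 8 shops, several of which may have none. The report should say so.

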#### mRDT quality survey

Suspected uncomplicated malaria cases aged 6 months and above in the intervention arm only

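### The mRDT quality survey's 591 counts suspected cases, but its 1% precision formula needs about 493 microscopy-positive cases, so the stated precision for sensitivity is not secured

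*Protocol article*

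**What the plan says.** In the Protocol article, under Sample size estimation, mRDT quality survey: "A minimum of 591 suspected uncomplicated malaria cases visiting OTCMS in the intervention clusters will be required". The basis given is "based on an estimated sensitivity of 98.7% (unpublished national data), 1% precision, 20% non-response rate, and 95% confidence level".

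Under Evaluation phase, mRDT quality survey, blood smears are prepared for eligible suspected cases, and "The microscopy results will be matched against mRDT results to determine the sensitivity, specificity, and predictive values of the mRDTs used". Microscopy is therefore the reference standard.

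Under Inclusion criteria, mRDT quality survey, the population is "Suspected uncomplicated malaria cases aged 6 months and above in the intervention arm only". Microscopy-positivity is not a condition of entry. The exclusions concern infants under 6 months, pregnancy and signs of severe disease.

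Under Secondary outcomes, sensitivity, specificity and predictive values of the tests form the last item listed. The document gives no expected share of microscopy-positive cases and no expected specificity.

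**The concern.** Sensitivity is the proportion of microscopy-positive patients whose mRDT is positive. Its denominator is the microscopy-positives, not everyone who walks into a shop with suspected malaria. A precision calculation built on an expected sensitivity therefore returns a number of positives. To turn that into a number of suspected cases, it has to be divided by the expected positivity. If that step is left out, the survey yields fewer positives than the formula assumed, and the interval for sensitivity is wider than stated.

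At stake is the precision that readers will credit to a named secondary outcome. The missing step cannot be treated as something left to a fuller document. The article gives every input, a result and a target, and the result does not secure the target.

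**Working it through.** **Inputs**, all from Sample size estimation, mRDT quality survey: expected sensitivity p = 0.987; half-width d = 0.01; "95% confidence level", so z = 1.96; "20% non-response rate"; stated size 591.

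**1. Reproduce the stated figure.**
n = z² p(1 − p) / d² = 3.8416 × 0.987 × 0.013 / 0.0001 = 492.9
492.9 × 1.2 = 591.5, which matches 591.
Dividing by 0.8 gives 616.1 and does not match. A one-sided z gives 347 before any allowance and does not match. Every stated input is used once, which leaves no room for a positivity term.

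**2. Positivity at which ±1 point is reached.**
The requirement is evaluable cases × positivity ≥ 493.
- All 591 evaluable: 493/591 = 0.834, so about 83%. That would leave 591 − 493 = 98 negatives.
- After 20% non-response: 591 × 0.8 = 472.8, about 473, which is below 493 at any positivity. At 100% positive the half-width is 1.96 × √(0.987 × 0.013 / 473) = 0.0102, or ±1.02 points.

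**3. Half-width over a range of positivity.**
The positivities are assumptions, because the document gives none. Half-width = 1.96 × √(0.987 × 0.013 / number of positives).

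| Assumed positivity | Positives of 473 | Negatives of 473 | Half-width, 473 evaluable | Half-width, 493 evaluable | Half-width, 591 evaluable |
|---|---|---|---|---|---|
| 20% | 95 | 378 | ±2.28 | ±2.24 | ±2.04 |
| 30% | 142 | 331 | ±1.86 | ±1.83 | ±1.67 |
| 50% | 236 | 236 | ±1.44 | ±1.41 | ±1.29 |
| 80% | 378 | 95 | ±1.14 | ±1.12 | ±1.02 |

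The 493 column applies if 617 are enrolled and 20% are lost.

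**4. Non-response allowance.**
To keep 493 after losing 20%, the enrolled number must be 493/0.8 = 616.25, so 617. Multiplying by 1.2 leaves 473. The difference is 617 − 591 = 26 cases. At 100% positivity it moves the half-width only from 1.00 to 1.02.

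**5. Size needed for ±1 point.**
Evaluable suspected cases = 492.9 / positivity; enrolled = that figure / 0.8.
- 20%: 2,465 evaluable, 3,081 enrolled
- 30%: 1,643 and 2,054
- 50%: 986 and 1,233
- 80%: 617 and 771

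**The case against.** The strongest case on the other side is about weight. The survey is single-arm and descriptive. It does not feed the primary outcome, the comparison between arms or the household survey's sample size. A sensitivity near 98.7% known to within about 2 points rather than 1 may support the same practical conclusion. All of that stands, and it limits how serious the point is.

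A reader might go further than the document allows in four ways.

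- **That the interval will be 1.4 to 2.3 times as wide as stated.** This rests on an assumed positivity of 50% down to 20%. The survey takes symptomatic patients in the peak transmission season, and at 80% the half-width would be about 1.1 points. The widening has to be stated conditionally.
- **That essentially every suspected case would have to be positive, leaving nobody for specificity.** This is true only after the full 20% loss. If all 591 were evaluable, about 83% would be enough. The document calls 591 a minimum and does not say whether non-responders are replaced.
- **That the interval would run past 100%.** This presupposes a simple normal-approximation interval. The document names no interval method for sensitivity, and that choice can properly sit in an analysis plan that is not shown.
- **That clustering by shop makes the precision worse still.** The document gives no intracluster correlation for test accuracy. Its 0.02 belongs to the household testing rate. No further widening can be claimed.

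None of this rescues the denominator. The formula gives positives, the plan counts suspected cases, and the plan itself expects some of them to be negative.

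**Conclusion.** The concern holds. The 591 is reproduced with no allowance for positivity, so it does not secure the ±1 point for sensitivity that is stated as its basis. That much needs no assumption: with the plan's own non-response the target is narrowly missed even if every case is positive, and with no loss at all it needs about 83% positive.

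The size of the shortfall does rest on an assumption. Between 80% and 20% positivity, the expected half-width with 473 evaluable cases runs from about 1.1 to about 2.3 points. The figures use the same normal-approximation formula as the plan and treat cases as independent, as the plan's own calculation does.

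The error in the non-response allowance is real but immaterial by itself. Overall this is a moderate issue: a wrong stated precision for a secondary outcome, with no bearing on the primary comparison.

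**What to change.** Keep the planned size and correct what is claimed for it.

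- Replace the 1% precision by the half-width expected for sensitivity over a stated range of positivity, with a source for the range if there is one. For 591 enrolled and 20% lost, that is about ±2.3, 1.9, 1.4 and 1.1 points at 20%, 30%, 50% and 80%.
- If the non-response allowance is also corrected and 617 are enrolled, quote about ±2.2, 1.8, 1.4 and 1.1 instead. The half-widths must match the number enrolled.
- State the expected precision for specificity from the microscopy-negatives (378, 331, 236 and 95 of 473 at the same positivities), using an expected specificity that the investigators supply.

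The cost is a change of wording and a less favourable stated precision, plus 26 more cases if the allowance is corrected. If ±1 point is truly required, the alternative is to recruit until about 493 evaluable microscopy-positives are reached. That is far more expensive at low positivity: about 2,054 enrolled at an assumed 30%.
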